#### Reliability analyses

In contrast to validity, reliability analyses have a relatively simpler task in answering the following question: are the reports of screening behavior on an initial survey congruent with a follow-up survey regardless of the accuracy of the behavior with respect to EMR data?

Test-retest reliability, the reproducibility of a measure [40], will be assessed for each type of cancer screening. We will code a participant’s responses as consistent if the time interval between the survey date and the self-reported month and year was within guidelines on both the validation and reliability surveys, or if no test within guidelines was reported on both surveys. Patients with a screening test documented in the EMR for a given cancer site between completion of the validity and reliability surveys, or who were up to date with screening at the time of the validity survey but not at the time of the reliability survey due to the passage of time, will be excluded from reliability analyses due to the possibility that their true cancer screening status may have changed.By cancer type and survey modality, we will use Cohen’s Kappa [41] statistic to assess repeatability while correcting for chance agreement between survey administration time points. Kappa coefficients >0.80 are often used to indicate *excellent* agreement while *Kappa* coefficients between 0.61 and 0.80 indicate *substantial* agreement [42]. For participants whose screening status changes during the period between the baseline and follow-up surveys (e.g., due to recently being screened), response concordance will be measured against the updated screening status. As with the validity analyses, we will also analyze reliability by the time of the last recorded screening examination in groups, such as within 6 months, 6 months to less than a year, etc., as well as by questionnaire modality (web vs. phone). That is, we will see if the reliability coefficients for an answer to recent screening depend on the length of time to the last screening examination.

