Breast	Individual decision to start screening every 2 years for women 40–49 years Screening every 2 years for women aged 50–74 years	Mammogram in 2 years before data pull	Breast, cervical, and colorectal: females ages 50–65 Breast and colorectal: females ages 66–74 Breast and cervical: females ages 40–49	Prior cancer diagnosis Do not speak English or Spanish*	
Cervical	Cytology screening every 3 years in people with a cervix aged 21–29 Cytology screening alone every 3 years for people with a cervix aged 30–65 OR HPV testing every 5 years for people with a cervix aged 30–65 OR Co-testing (cytology plus HPV testing) every 5 years for people with a cervix aged 30–65	Cytology alone in 3 years before data pull OR HPV testing (with or without cytology) in 5 years before data pull	Cervical-only: females ages 21–39	Prior cancer diagnosis Prior hysterectomy Did not speak English or Spanish*	
Colorectal	FOBT or FIT test every year for adults aged 45–75 years OR FIT-DNA test every 3 years for adults aged 45–75 years OR Sigmoidoscopy every 5 years for adults aged 45–75 years OR Sigmoidoscopy every 10 years plus annual FIT for adults aged 45–75 years OR CT colonography every 5 years for adults aged 45–75 years OR Colonoscopy every 10 years for adults aged 45–75 years	FOBT or FIT in 1 year before data pull OR Sigmoidoscopy or colonoscopy within 5 years before data pull	Colorectal-only: males and females ages 50–75	Prior cancer diagnosis Prior colectomy Adults ages 45–49 Do not speak English or Spanish*	We do not include adults ages 45–49 despite USPSTF screening recommendations because health care systems are in the process of adopting this new recommendation during the study period. We will not look back for 10 years for colonoscopy history because this would limit our eligible sample to a very select population.
Lung	LDCT every year in adults aged 50–80 years who have a 20 pack-year smoking history AND currently smoke or quit within the past 15 years	LDCT in 1 year before data pull	Lung-only: males and females ages 55–75 with 30+ pack-year smoking history	Prior cancer diagnosis <30 pack-year smoking history Do not speak English or Spanish*	We do not include adults with a 20–29 pack-year history of smoking or those 55 and younger) despite USPSTF screening recommendations because health care systems were in the process of adopting this new recommendation during the study period.

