For sensitivity, specificity, PPV, NPV, and concordance we will calculate 95% confidence intervals based upon the binomial distribution. Sensitivity and specificity indicate the effectiveness of a test (here the NHIS survey result) with respect to a trusted “outside” referent, while PPV and NPV indicate the effectiveness of a test (the NHIS survey result) for categorizing people as having or not having a target condition/screening [37].

We will also calculate the report-to-records ratio, the ratio of participants reporting a test (true positives plus false positives) divided by the percentage of tests in the record (true positives plus false negatives). The report-to-records ratio is a measure of net bias in test reporting, where values >1.0 denote overreporting and values <1.0 denote underreporting [38]. All measures will be calculated for each cancer screening test type, as well as by mode of survey administration. For reports to records ratio, 95% confidence intervals will be generated using bootstrap resampling [39].

In our analysis, we will compare our accuracy measures for those completing the survey by web vs. phone. Because survey modality (phone vs. web) was randomly allocated, and we allow participants to change their mode of completion when we contact them, we will perform both an intent-to-treat analysis as well as a separate analysis by modality used.

For responses to the question ‘when did you have your most recent test to check for [cervical/breast/colorectal/lung] cancer’, we hypothesize response accuracy will vary based on the length of time since the last screening exam. We will present the proportion of patients who answer ‘yes’ to having had screening stratified by ranges of time between the survey date and time of last screening exam, including a stratum for those who have not had this exam within the study reporting period of 5 years. In addition, we will present the proportion of patients who had screening exams, within these ranges of time, among those who answer ’yes’ or ’no’ to each question. All analyses will be stratified by cancer site.

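### Retest consistency is scored against each survey's own date, so identical answers can be coded inconsistent, and the passage-of-time exclusion only partly prevents this

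*Protocol article*

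**What the plan says.** The Reliability analyses section asks whether two reports agree "regardless of the accuracy of the behavior with respect to EMR data". The first way for a pair of answers to count as consistent reads: "if the time interval between the survey date and the self-reported month and year was within guidelines on both the validation and reliability surveys". A pair with no in-guideline test in either survey also counts. One report inside guidelines and one outside is therefore inconsistent.

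Two groups are removed: people with an EMR-documented test between the surveys, and those "who were up to date with screening at the time of the validity survey but not at the time of the reliability survey" because time has passed. The reason given is "due to the possibility that their true cancer screening status may have changed". Later in the same section, people whose status changes between surveys are to have their agreement judged by their new status, which presupposes that they stay in the analysis.

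The gap is 1 or 3 months. It is randomized at three sites and assigned by recruitment wave at Henry Ford Health, which recruits for lung screening only. Kappa is planned by cancer type and survey modality, and reliability also by time since the last recorded exam. The windows in Table 2 are 12 months for lung, 24 for breast, 36 or 60 for cervical, and 12 or 60 for colorectal.

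**The concern.** Reliability is meant to compare one report with another. Under this rule the second report faces a cut-off that has moved by the length of the gap. A respondent who dates a low-dose CT to 11 months before the first survey and names the same month three months later is inside the 12-month window the first time and outside it, at 14 months, the second. The two answers are identical and the coding says they disagree.

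The exclusion rescues this person only if the EMR also shows a lapse between the surveys. If the EMR dates the scan to 8 months before the first survey (up to date at both), to 13 months before (up to date at neither), or has no scan, the person stays in and counts against reliability. The article expects such discrepancies: it discusses over-reporting, missing home stool tests and telescoping. Agreement between two reports then depends on agreement with the EMR, which the section says it should not.

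At stake is a kappa that understates repeatability, more at 3 months than at 1, and most for annual tests. Unequal exclusion between the two gaps adds a further difference.

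**Working it through.** The article gives no figure for this effect, so there is none to reproduce.

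**Inputs from the article.** Gap g = 1 or 3 months; window L = 12, 24, 36 or 60 months.

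**Assumptions.** Exam dates are uniform over 60 months. Reported date = EMR date + normal error with the SD shown. Every person gives exactly the same date twice, so true reliability is perfect.

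**Step 1: no exclusion.** With reported dates uniform inside the window, the share of in-window reporters who cross the cut-off is g/L.

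| L (months) | 1 month | 3 months |
|---|---|---|
| 12 | 1/12 = 8.3% | 3/12 = 25.0% |
| 24 | 1/24 = 4.2% | 3/24 = 12.5% |
| 36 | 1/36 = 2.8% | 3/36 = 8.3% |
| 60 | 1/60 = 1.7% | 3/60 = 5.0% |

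These shares still apply to people who report an in-window exam that the EMR lacks, because an EMR-based exclusion never reaches them.

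**Step 2: what the exclusion removes.** By the same formula it drops g/L of EMR up-to-date people. For a 12-month window that is 8.3% at 1 month and 25% at 3 months.

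**Step 3: what remains after an EMR-based exclusion.** This was simulated. The table shows the share of retained first in-window reporters who are coded inconsistent.

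| L (months) | Error SD (months) | 1 month | 3 months | Kappa, 1 vs 3 months |
|---|---|---|---|---|
| 12 | 0 | 0% | 0% | 1.00 vs 1.00 |
| 12 | 1 | 5.5% | 8.5% | 0.97 vs 0.95 |
| 12 | 2 | 7.1% | 15.2% | 0.95 vs 0.90 |
| 12 | 4 | 7.8% | 21.1% | 0.95 vs 0.86 |
| 24 | 4 | 3.9% | 9.7% | 0.97 vs 0.92 |

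As a share of everyone analysed, the SD 4, 12-month row is 1.5% vs 3.7%.

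**Step 4: sensitivity.** If one third of the sample is up to date, one third was screened earlier and one third has no exam, kappa at SD 4 and L = 12 is 0.96 vs 0.89. In that mix, the 3- to 1-month ratio of inconsistent shares among all analysed is about 1.3 at SD 1, 2.2 to 2.3 at SD 3 and 2.6 to 2.7 at SD 6. Adding half a month of contact delay to each gap lowers these to about 1.1, 1.7 to 1.8 and 2.0 to 2.1.

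**Step 5: fixed reference date.** If both reported dates are measured from the first survey, identical dates always fall on the same side of the cut-off. The artefact is 0% at both gaps and kappa is 1.00.

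**The case against.** The authors foresaw date drift and wrote an exclusion for it. The words tying status to the EMR are attached only to the between-survey test; the passage-of-time limb names no data source. If it also covers lapse of the self-reported date, the artefact disappears. That reading is possible, but the stated reason speaks of true status, which points to the EMR. It would also still drop g/L of in-window reporters, unevenly between the gaps.

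The sizes are modest and conditional. Every kappa above stays over the 0.80 that the plan cites for excellent agreement, and only lung has a purely annual definition. This stands and limits the weight of the point.

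Three stronger readings do not hold:

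- A reader might infer that the artefact is always two to three times larger at 3 months. That depends on dating errors of about 2 months or more, or on reports absent from the EMR.
- A reader might infer that a planned 1- vs 3-month comparison would be spoiled. The article names no kappa by gap. The gap is nonetheless assigned as part of the reliability design, and the planned analysis by time since last exam is exposed near the cut-off.
- A reader might infer from Table 2 ("LDCT in 1 year before data pull") that validity suffers in the same way. Those definitions fit the sampling strata, while the Validation section takes EMR data before each survey and the primary validity analysis is "stratified by ranges of time between the survey date and time of last screening exam". Nothing freezes the validity standard at the data pull.

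**Conclusion.** The point holds as a flaw in the reliability coding. The rule lets the cut-off move with the retest date, and the exclusion, on its natural reading, corrects this only where reported and EMR dates agree. The same section also both excludes and retains people whose status changes, and these instructions must be reconciled.

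For the lung window the artefact runs from zero with no dating error to about 8% vs 21% of retained first in-window reporters at SD 4 months. It is smaller for longer windows. These figures rest on uniform exam dates and an assumed dating error. They show a bias worth removing; they do not suggest that the reliability results would be unusable.

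**What to change.** In the reliability analysis, class the dates reported in both surveys against the first-survey date. Exclude only people with an EMR-documented test between the surveys. Delete the passage-of-time exclusion, and delete the sentence on updated status or reconcile it with the remaining exclusion.

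The cost is a change to a coding rule. All dates are already collected, and participants who would have been excluded return to the analysis.

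There is one small downside. Respondents who answer by elapsed time (about 13 months ago, both times) imply a later calendar date at the second survey, and a fixed reference can code some of them inconsistent. If everyone answered that way, the 12-month, SD 4 case would show 1.7% vs 5.0% of all analysed inconsistent and kappa of 0.95 vs 0.86. The plan's rule is built on a reported month and year, so the fixed date is the better primary choice. The survey-date version can be kept as a sensitivity analysis.

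### The reliability section gives two incompatible rules for participants whose screening status changes between surveys: one excludes them, the other keeps them in a comparison that measures validity

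*Protocol article*

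**What the plan says.** All of the relevant text is in the Reliability analyses section of the protocol article.

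- **Aim.** The section asks whether the first and second reports of screening agree "regardless of the accuracy of the behavior with respect to EMR data". Consistency is coded from the two self-reports only: a within-guideline test reported both times, or none reported both times.
- **Exclusion rule.** It has two limbs. The first is "Patients with a screening test documented in the EMR for a given cancer site between completion of the validity and reliability surveys". The second is those "who were up to date with screening at the time of the validity survey but not at the time of the reliability survey", because time has passed. Both groups "will be excluded from reliability analyses due to the possibility that their true cancer screening status may have changed".
- **Statistic.** Cohen's kappa, by cancer type and survey modality, is the "statistic to assess repeatability while correcting for chance agreement between survey administration time points".
- **Later rule.** "For participants whose screening status changes during the period between the baseline and follow-up surveys (e.g., due to recently being screened"), the plan is that "response concordance will be measured against the updated screening status".

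**The concern.** The example in the later rule, people recently screened, is the first group that the exclusion rule removes. An analyst who follows the exclusion sentence has nobody left to whom the later sentence could apply. One who follows the later sentence has not excluded them.

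The later rule also asks a different question. Comparing an answer with a person's updated status tests whether the answer is right. Test-retest reliability asks whether two answers match, and the section explicitly sets accuracy aside.

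What is at stake is who is counted in the reliability results and what the coefficient means. If the choice is left open, it could be made after the data have been seen. Status changes also accumulate with time, so the rule chosen affects 3-month retests more than 1-month retests.

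**Working it through.** **1. The two rules side by side**

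| | Exclusion rule | Later rule |
|---|---|---|
| Who | New EMR test between surveys, or lapsed status | Status changed between surveys, for example through a recent screen |
| Treatment | Removed from reliability analyses | Response scored against updated status |
| Comparison | Survey 2 with survey 1, in those remaining | Response with actual status |

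The groups overlap and the treatments exclude each other. Neither this section nor Missing data labels one rule as primary and the other as a sensitivity analysis.

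**2. The plan's own figure.** Sample size gives 1,260 (80%) retests out of 1,576 participants: 0.80 × 1,576 = 1,260.8, so the figure reproduces. It is stated as the number to be included in the reliability assessment. Whether status-changers count towards it depends on which rule is used.

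**3. How many people lapse**

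Inputs: retest gaps of 1 and 3 months (Design) and the up-to-date windows in Table 2, which are 1 year for LDCT and FOBT/FIT, 2 years for mammography, 3 years for cytology alone, and 5 years for HPV testing and endoscopy. Assumptions that the document does not give: exam dates spread evenly over the window, no rescreening, half of retested people up to date, and an even split between 1 and 3 months.

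Share of up-to-date people who lapse = gap ÷ window. Share of all retests affected = 0.5 × the mean of the two lapse shares.

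| Window | Lapse in 1 month | Lapse in 3 months | Share of all retests |
|---|---|---|---|
| 1 year | 1/12 = 8.3% | 3/12 = 25% | 0.5 × 16.7% = 8.3% |
| 2 years | 1/24 = 4.2% | 3/24 = 12.5% | 0.5 × 8.3% = 4.2% |
| 3 years | 1/36 = 2.8% | 3/36 = 8.3% | 0.5 × 5.6% = 2.8% |
| 5 years | 1/60 = 1.7% | 3/60 = 5% | 0.5 × 3.3% = 1.7% |

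People newly screened between surveys are not counted here and form a further affected group.

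**4. What the rule could do to kappa, if it were applied there**

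Illustrative assumptions: kappa of 0.70 in people with stable status, half of answers positive, and 10% status-changers, half gained and half lapsed. With even margins, chance agreement is 0.5 and kappa = 2 × agreement − 1. Stable agreement is therefore 0.85. Let *a* be the accuracy of the changers' answers.

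- Excluding changers: kappa = 2 × 0.85 − 1 = 0.70.
- Scoring changers against updated status: agreement = 0.9 × 0.85 + 0.1 × *a*. For *a* = 95%, 80% and 60% this is 0.860, 0.845 and 0.825, so kappa is 0.72, 0.69 and 0.65.
- For comparison, keeping changers as ordinary test-retest pairs (neither written rule): their agreement is 2*a*(1 − *a*), and kappa is 0.55, 0.59 and 0.63.

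Under the later rule the coefficient would move with recall accuracy, which the section says should play no part.

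**The case against.** The best defence is that the kappa population is in fact stated. The exclusion sentence is explicit, gives its reason and comes directly before the kappa sentence. The later sentence speaks of response concordance, not kappa. In the validity section that word means percentage agreement with the record, whereas kappa is described as agreement between survey time points. On that reading, kappa uses those not excluded, and status-changers get a separate concordance figure. The reading is possible, but the text does not state it: the sentence sits in the reliability section after the kappa description, and no separate analysis is defined.

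The defence does limit what can be claimed. A reader might infer any of the following, and the document supports none of them as a settled fact:

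- **That validity error will enter kappa.** This is one reading of the later sentence, not a stated plan.
- **That the rule scores answers against the EMR in so many words.** The text says updated status. The EMR is the natural reading, because new tests are identified there and it is the study's gold standard, but this is an inference.
- **That a planned 1- versus 3-month comparison is distorted.** Kappa is specified by cancer type, modality and time since last exam. Retest interval is randomised (except at Henry Ford Health, where it went by selection wave), but this section specifies no comparison of kappa between intervals.
- **That about 8% applies to every cancer.** It is the figure for one-year windows. Colorectal status can also rest on endoscopy within 5 years, and the breast and cervical windows are longer.

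**Conclusion.** The point holds as a conflict between two stated rules, so it is more than detail left to a fuller document. The section both excludes and retains people whose status changed, and the retaining rule is a validity comparison at odds with the section's own definition of reliability.

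Under the assumptions listed, lapse alone touches about 8% of retests for one-year windows and about 2% to 4% for two- to five-year windows. Within each window, the share at 3 months is three times that at 1 month. The effect on kappa is conditional on the later rule being applied there. In the illustration kappa runs from 0.65 to 0.72 against 0.70, so neither written rule takes it below the 0.61 benchmark. The case therefore rests on the population and meaning of the coefficient, not on a predicted change of conclusion. The primary validity analyses are unaffected.

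**What to change.** - Keep the existing exclusion sentence as the single population rule for kappa, with both limbs: a new EMR-documented test and lapse through time. The lapse limb is needed. Under the consistency coding, someone who correctly gives the same exam date twice, but crosses the window in between, would otherwise be scored as inconsistent.
- Delete the sentence that scores responses against updated status, or move it to a separately labelled secondary validity analysis of the second survey. State that this analysis does not enter kappa, and name the source of the updated status.
- Report the numbers excluded under each limb by follow-up interval, for each cancer site.

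The cost is a change of one or two sentences in the protocol and analysis plan, made before the reliability data are analysed. No further data are needed, since the exclusion rule already requires EMR tests between surveys to be identified.

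### Cohen's kappa is not comparable across groups defined by time since the last recorded exam, so it should not carry the recency comparison of reliability on its own

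*Protocol article*

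**What the plan says.** All of this is in the protocol article.

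- **Coefficient.** Under Reliability analyses, by cancer type and survey mode, "we will use Cohen’s Kappa [41] statistic to assess repeatability while correcting for chance agreement between survey administration time points". No other reliability coefficient is named.
- **Rated answer.** A respondent is coded consistent when "the time interval between the survey date and the self-reported month and year was within guidelines on both the validation and reliability surveys". Reporting no such test in either survey also counts. The answer compared is therefore binary.
- **Recency breakdown.** The plan is to "analyze reliability by the time of the last recorded screening examination in groups, such as within 6 months, 6 months to less than a year" and so on. The stated purpose is: "we will see if the reliability coefficients for an answer to recent screening depend on the length of time to the last screening examination".
- **Change of status.** People with a new recorded test between surveys, or who lapse from up to date through the passage of time, "will be excluded from reliability analyses due to the possibility that their true cancer screening status may have changed".
- **Guideline status.** Table 2 (Participants section) defines it by time since the exam, for example "Mammogram in 2 years before data pull" for breast and "LDCT in 1 year before data pull" for lung. For cervical (3 or 5 years) and colorectal (1 or 5 years) it also depends on the type of test.

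**The concern.** The grouping variable, time since the recorded exam, is also what determines whether yes or no is the correct answer. A group such as within 6 months is up to date at every cancer site, so most of its members should answer yes. Groups past the guideline interval will contain many fewer yes answers. Kappa corrects for chance using each group's own margins. Its value therefore moves with the share answering yes even when the share of people who change their answer does not.

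At stake is the meaning of the recency comparison. A lower kappa in the recent groups could be read as poorer repeatability for recent exams when it reflects only lopsided margins. That gradient would run against the loss of recall over time that the study sets out to describe.

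**Working it through.** **1. The plan's own reliability figure.** The Sample size section gives 1,260 participants as 80% of 1,576: 0.80 × 1,576 = 1,260.8, which agrees. It claims power above 0.80 to rule out kappa below 0.61 if true agreement exceeds 70%. I read 70% as kappa 0.70, because 70% raw agreement at 50/50 margins gives kappa (0.70 − 0.50)/0.50 = 0.40, below the null. The large-sample variance for a binary rating with equal margins is

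n·var = (1−κ)[(1−κ)(1−2κ) + κ(2−κ)/(2p(1−p))].

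Alpha is not stated; I took 0.05. Power at n = 1,260:

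| Share answering yes, p | One-sided | Two-sided |
|---|---|---|
| 0.50 | 0.996 | 0.989 |
| 0.80 | 0.957 | 0.914 |
| 0.90 | 0.791 | 0.678 |
| 0.95 | 0.533 | 0.396 |

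The claim is reproduced for moderate margins. Precision falls away at lopsided ones, even with the full sample.

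**2. How kappa depends on the margin.** Let p be the share answering yes on each survey and d the share who change their answer. Observed agreement is 1 − d and chance agreement is p² + (1−p)² = 1 − 2p(1−p), so

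κ = 1 − d / (2p(1−p)).

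**3. Margins implied by Table 1.** The mammography meta-analysis row gives sensitivity 0.96 and specificity 0.61. With a recent exam p ≈ 0.96, so 2p(1−p) = 0.0768. Without one p ≈ 1 − 0.61 = 0.39, so 2p(1−p) = 0.4758. These are averages over all screened and all unscreened women, used here to stand for a recent and a no-recent-exam group.

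**4. Same consistency, different kappa.** The article gives no retest rates, so d is assumed over a range.

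| Raw agreement | d | κ at p = 0.96 | κ at p = 0.39 |
|---|---|---|---|
| 96% | 0.04 | 1 − 0.04/0.0768 = 0.48 | 1 − 0.04/0.4758 = 0.92 |
| 97% | 0.03 | 0.61 | 0.94 |
| 99% | 0.01 | 0.87 | 0.98 |

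**5. What specific agreement shows.** Positive specific agreement is 1 − d/(2p) and negative is 1 − d/(2(1−p)). At d = 0.04 the recent group has 1 − 0.04/1.92 = 0.98 and 1 − 0.04/0.08 = 0.50. The other group has 1 − 0.04/0.78 = 0.95 and 1 − 0.04/1.22 = 0.97. The low kappa in the recent group comes from its few no answers.

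**6. If errors are independent between surveys.** With sensitivity 0.96, a group that is entirely up to date has agreement 0.96² + 0.04² = 92.3% and kappa 0.00. With 98% up to date (specificity 0.61), agreement is 91.5% and kappa 0.13. A 50/50 mix has lower agreement, 72.4%, but higher kappa, 0.37.

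**7. If misreports persist within a person.** With within-person error correlation ρ and constant true status, d = 2p(1−p)(1−ρ), so κ = ρ. At p = 0.96, ρ = 0.7 gives κ = 0.70 with 97.7% agreement, and ρ = 0.9 gives κ = 0.90 with 99.2%.

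**8. Precision within a group (assumed sizes).** Simulated with p = 0.96 and d = 0.04, the 95% range of kappa at n = 100 is −0.03 to 0.86. At n = 50 kappa is undefined in about 4% of samples. With p = 0.39, d = 0.04 and n = 100 the range is 0.83 to 0.98.

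**The case against.** A reader might infer that true status is constant within a recency group, that kappa must therefore collapse in both the newest and the oldest groups, and that the analysis is invalid. The documents do not support that.

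- **Answers matter, not true status.** Near-constant reported answers pull kappa down at high agreement. Mammography specificities in Table 1 run from 0.506 to 0.78, implying roughly 22% to 49% yes among women without the test. Those groups need not collapse, as the 0.92 above shows. For stool tests the pattern can differ: one FIT/FOBT row has specificity 0.96, or about 4% yes among the unscreened, so there the distortion would fall in the older groups.
- **Some groups mix statuses.** Cervical and colorectal intervals depend on test type, and a group can straddle a cut-off.
- **A kappa of exactly zero needs independent errors** in two surveys taken 1 to 3 months apart in the same mode, which is extreme. Kappa remains defined as persistence of individual answers. If that is the question and status is constant, it is raw agreement that moves with the margin: at ρ = 0.7 it is 97.7% at p = 0.96 and 85.7% at p = 0.39.
- **Benchmarks.** The text sets out 0.61 and 0.80 beside the analysis by cancer type and mode. It does not say they will grade recency groups.
- **Reach.** The breakdown is additional and descriptive. Recall over time is also studied by proportions answering yes and by a regression of correct answers on recency. The authors themselves say that usual concordance measures may need rethinking.

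These points limit the concern but do not remove it. The section's stated question is whether the two reports match, which raw agreement answers directly. Cohen's kappa is the only coefficient named when the text says reliability coefficients will be compared, and the other recency analyses concern validity. The caution about prevalence under Limitations is about sensitivity and specificity, not kappa.

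**Conclusion.** The concern holds in a limited form. Read alone, kappas from different recency groups do not compare answer consistency. On the margins implied by Table 1 for mammography, equal raw agreement of 96% gives 0.48 against 0.92. At 99% the gap narrows to 0.87 against 0.98. The distortion is largest where nearly everyone gives the same answer, mainly the recent groups, and can make recent exams look less reliable than older ones.

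That kappa varies with the margin is algebra. Its size rests on assumptions: retest change of 1% to 4%, equal margins on the two surveys, and average sensitivity and specificity standing in for group margins. It is smaller if few people change their answers, as when misreports are stable within a person, and less clear-cut where groups mix statuses. None of this makes kappa invalid, and it does not touch kappa as the main statistic in the pooled analysis by cancer type.

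**What to change.** In Reliability analyses, state that the comparison by time since the last recorded exam rests on raw agreement, which is the mean of the consistent/inconsistent coding already defined. Report it with positive and negative specific agreement, each with a 95% confidence interval. Show kappa only beside these, and do not rank recency groups by kappa alone. Keep Cohen's kappa as the main statistic for the pooled analysis by cancer type. A prevalence-adjusted index such as Gwet's AC1 may be added but is not needed.

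The cost is a sentence or two of wording and a few extra statistics from the same 2×2 tables, with no new data. The trade-off is that the usual kappa benchmarks are not used to grade recency groups, and that raw agreement is not corrected for chance, which is why the specific agreements and kappa are shown with it.
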